## Abstract

**Background:**

Iodine is a key component of thyroid hormones that are critical for normal development of the brain and nervous system in utero. Recent results indicate that two thirds of pregnant women in Europe have sub-optimal iodine nutrition. In Norway, milk and seafood are the most important dietary iodine sources and contributes to about 80% of the intake.

**Method:**

Two-armed randomized trial where 137 pregnant women were randomized to either receiving cod twice weekly, or continue with habitual diet for 16 weeks (pregnancy week 20–36). Socioeconomic- and demographic factors, dietary information and biological (urine, blood, and hair) samples are collected pre- and post-intervention, and at six weeks, three-, six-, and eleven months postpartum. Biological samples (urine, blood, and hair) of the infant are collected at six weeks, three-, six-, and eleven months postnatal. Child development is assessed by The Bayley Scale of Infant and Toddler Development, 3rd edition, at eleven months, and by parent report on the Ages and Stages Questionnaire, 3rd edition, and Ages and Stages Questionnaire: Social Emotional at three-, six-, and eleven months.

**Discussion:**

The Mommy’s Food study will provide knowledge on changes in iodine nutrition when consuming iodine rich fish during pregnancy and contribute to the understanding of the impact of iodine status in pregnancy on infant neurodevelopment.

**Trial registration:**

This study is registered in ClinicalTrials.gov (NCT02610959). Registered November 17, 2015.

## Background

Iodine is an essential nutrient for the synthesis of thyroid hormones triiodothyronine (T_3_) and thyroxine (T_4_). Dietary iodine is rapidly absorbed through the stomach and duodenum, and the thyroid gland is dependent on regular and adequate supply through the diet in order to produce these vital thyroid hormones. Thyroid hormones are involved in a range of biochemical processes, including regulation of metabolic rate, energy production, protein and enzyme synthesis, thermoregulation, growth and neural development [1].

The iodine requirement during pregnancy is greatly increased because the mother synthesizes approximately 50% more T_4_ to maintain maternal euthyroidism and to transfer thyroid hormones to the fetus prior to gestational week 20, and because iodine needs to be transferred to the fetus for fetal thyroid hormone production post gestational week 20. In addition, the renal iodine clearance increases during pregnancy. Thus, it is important for pregnant women to consume sufficient iodine during pregnancy [1].

In general, we have limited dietary iodine sources and the iodine content of terrestrial foodstuffs is much lower compared to marine foodstuffs. The only good natural source of iodine is seawater fish and other marine products [2]. Iodized salt is the most important source worldwide and is also the agreed strategy for achieving iodine sufficiency [2]. In Norway, iodized salt contributes insignificantly as the maximum level of iodine added to salt is 5 μg/g, and the food industry is not permitted to use iodized salt.

Pregnant and lactating women are vulnerable groups in terms of developing iodine deficiency since they have higher needs of iodine [2, 3]. This has been confirmed in the most recent data from the Norwegian Mother and Child Cohort Study (MoBa) (*n* = 61,904), demonstrating inadequate iodine intake in the majority of pregnant Norwegian women. The median iodine intake was 141 μg/day from food and 166 μg/day from food and supplements. Only 21.7% reach the recommended daily intake by WHO/UNICEF/ICCIDD of 250 μg iodine/day, and the study concludes that suboptimal iodine intake among Norwegian pregnant women is a health concern [4]. Determination of iodine status by urinary iodine concentration (UIC) in a sub-study of the MoBa (*n* = 119) was in line with the findings from the dietary study [4], and insufficient iodine status has also been demonstrated in other studies among Norwegian pregnant women [5, 6].

Inadequate iodine status in pregnancy has been associated with suboptimal cognitive outcomes in the children at eight years of age in observational studies [7]. This in line with the MoBa study where maternal iodine intakes below the Estimated Average Requirements (160 μg/d) during pregnancy was associated with child language delay, impaired fine motor skills and mental health problems at three years of age, but no associations with gross motor skills as measured [8]. Interestingly, the results showed no evidence of a protective effect of iodine supplementation during pregnancy on child development. Few intervention studies on maternal iodine supplementation on child development exist and the quality of the existing studies are poor, as concluded in a recent review [9]. To our knowledge, this is the first trial intervening pregnant women with iodine rich foods (cod), to study its effects on maternal iodine status and infant development.

## Methods/design

The overall aims of this trial are to investigate, in a randomized controlled trial (RCT), if an increased intake of cod in pregnancy has an impact on (1) maternal iodine status and (2) infant development.

### Trial design

The study is a two-armed randomized controlled intervention trial involving cod intake in pregnancy with the primary purpose of prevention. The ideal control would be pregnant women from the same trial whom were to be instructed to continue with their habitual diet with restriction to include iodine. For ethical reasons the control is pregnant women, within the same trial, who will continue with their habitual diet. The primary outcome is UIC measured at post intervention (gestational week 36), and the secondary outcome is neurodevelopment assessed by the cognitive, language and motor scales of the Bayley Scales of Infant and Toddler Developmental 3rd edition (Bayley-III) when the infants are 11 months of age. Other outcomes include urine samples, dietary data and blood samples from the mother and from the infant, as well as data on child development such as developmental status, socio-emotional abilities and infant sleep, and maternal mental health, that will be collected at several time points during the first year of life.

### Study setting and recruitment

Participants were recruited through the Women’s clinic at Haukeland University Hospital in Health region west in Norway. Approximately 5000 women give birth at the Women’s Clinic every year, which is the local hospital for the population in Bergen and surrounding areas. From January 2016 until February 2017, information regarding the intervention trial was included in the postal mail, sent from the Women’s Clinic, with the date/time for the routine ultrasound (RU). In Norway, the RU takes place in gestational week 17–19. To ensure sufficient participants information regarding the trial and invitation to participate was also broadcasted online (Facebook, Instagram, and magazine for pregnant in Norway). Pregnant women who were interested in the study contacted the secretariat. Time schedule of enrolment, interventions, assessments, and all visits for participants is schematically diagrammed in Fig. 1.

**Fig. 1 Fig1:**
[figure not shown]
Overview of study schedule and main activities. *Six consecutive days between GW 18 and GW 19 and between GW 35 and GW 36 (last days of intervention meal). †Questionnaire includes: participant characteristics; self-reported maternal mental health; and parent-reported infant mental health. Abbreviations: GW, gestational week; M, mother; I, infant; U, urine; S, serum; T4, thyroxine; T3, triiodothyronine; RBC, red blood cells; FA, fatty acids; H, hair; FFQ, Food Frequency Questionnaire; ASQ-3, The Ages and Stages Questionnaire; ASQ:SE, The Ages and Stages Questionnaire: Social Emotional; BISQ, Brief Infant Sleep Questionnaire; EPDS, The Edinburgh Postnatal Depression Scale; HADS, The Hospital Anxiety and Depression Scale. ^‡^Screening tool for eating disorders

### Eligibility criteria

Inclusion criteria: prim parous singleton pregnancy ≤ gestational week 19, Norwegian speaking and/or understand Norwegian writing (all validated tests of the child will be in Norwegian). Exclusion criteria: allergies to fish, chronic diseases known to affect iodine status (Graves’ disease, Thyroiditis, Thyroid Nodules, known hypothyroidism or hyperthyroidism).

### Randomization, allocation and blinding

Randomization will be performed individually by lottery at the second visit in gestational week 19 in blocks of 10 to ensure approximately equal allocation to the two study groups. Study investigators will enroll participants, generate the allocation, and randomly assign participants to interventions after baseline sampling. The study id-number for each participant will be a random number between 1 and 200. By this procedure, participants and investigators will be blinded to the allocation until the baseline sampling has been completed. Owing to the nature of the intervention, blinding of the participating mothers will not be possible. However, the infants will be blinded throughout the trial and data analysis and study investigators and laboratory personnel will be blinded when analyzing data.

### Dietary intervention

#### Study foods and instructions

Participants in the intervention group will receive frozen cod fillets (Lerøy A/S, Bergen, Norway) and are asked to consume two intervention meals of 200 g weekly (a total of 400 g cod per week). They will prepare the dinner meal themselves and are free to choose recipes. However, they will be provided with recipes that could be used ad libitum. For compliance purposes, participants will be instructed to weigh (Kitchen Scale, article no. 34–1207-16, ClasOhlson.com) the cod fillet before preparing the meal, and weigh the fillet leftovers (if any), after the meal is completed. The participants will record these data, in addition to receipt used and date of consumption, in a weight registration form. These data will be used in order to calculate iodine intake from the intervention meal. The participants in the control group will be instructed to follow their habitual diet. Once a pregnant woman is enrolled or randomized, the study investigators will make every reasonable effort to follow the participant for the entire study period. Prior to all the visits, the participants will be reminded about the upcoming appointment. Study investigators will always take into account the participants’ private calendar in the attempt to best ensure retention.

#### Safety of foods

Women in the intervention group will have an intake of (0.4 kg cod per week * 0.04 mg Hg/kg *1000=) 16 μg mercury (Hg) per week from the study diet. Weekly intake of dioxin and dioxin-like polychlorinated biphenyls (dl-PCBs) will be (0.4 kg per week *0.08 ng toxic equivalences (TEQ) /kg* 1000=) 32 pg TEQ per week. The CONTAM panel in the European Food Safety Authority (EFSA) established a tolerable weekly intake (TWI) for organic Hg of 1.3 μg/kg bodyweight. This is in accordance with the Joint FAO/WHO expert Committee on Food additives (JECFA) [10]. The equivalent TWI for dioxin and dl-PCB is 14 pg TEQ per kilo bodyweight [11]. For the participants in the study, their TWI is calculated based on the 5-percentile weight of the women in the Little in Norway cohort, *n* = 828 (unpublished data) (5 percentile = 56 kg). That means that they have a TWI of 71.2 μg Hg per week and 784 pg TEQ for dioxin and dl-PCBs. Thus, the intake of Hg and dioxins and dl-PCBs will be maximum 22% and 4% of the TWI. Consequently, the intake of cod in this study is far below the TWI for this especially vulnerable population.

### Assessment and data collection

#### Biological samples-urine

Participants will receive six marked tubes for collection of urine in gestational week 18–19 and in week 35–36 together with instructions on how to collect the spot urine samples. A pooled sample of 1 ml of homogenized spot urine collected on six consecutive days, between 4 pm and midnight, will be analyzed for iodine pre- and post intervention in both groups. The participants will keep the urine samples in their home freezer until the visits in gestational week 19 and 36. At this visits at three and six months postpartum, the mothers will deliver a spot urine sample. For the infants, urine collection pads will be placed in the diapers 1–2 h before the visit for urine sampling, and extracted at the visit at three-, six and eleven months. The urine samples will be transferred to cryo tubes and stored at minus 20 °C pending analysis by inductively coupled plasma mass spectrometry (ICP-MS). Method description of UIC (μg/L) determination is previously described by Dahl et al. [12]. Urinary creatinine concentration (g/L) will be analyzed using MAXMAT PL II multidisciplinary diagnostic platform with a creatinine PAP kit [13].

#### Biological samples-blood

Pre- and post-intervention blood sampling (gestational week 18 and 36) will include thyroid hormone status (thyroid stimulating hormone (TSH), free T_3_, free T_4_), fatty acid status, iron status and vitamin B_12_ status. The same blood sampling will be conducted in mothers and infants at three- and six months postpartum. Venous blood for serum preparation will be collected in BD Vacutainer® SST™ vials II *Advanced* and set to coagulate for minimum 30 min before centrifuging (1000–1300 G, 20 °C, 10 min) within 60 min. Venous blood for plasma preparation will be collected in BD Vacutainer® K2E 5.4 mg (adults) and 3.6 mg (infants) vials and centrifuged (1000–1300 G, 20 °C, 10 min) within 30 min, for the preparation of erythrocytes. Erythrocytes will be adequately separated from plasma and the layer on top of the cells (buffy coat) to ensure a clean erythrocyte fraction. In cases were venipuncture of infants will be problematic, capillary blood will be collected from the heel or a fingertip, depending on age/weight. Prior to capillary blood sampling, the heel or finger will be warmed with a hot water balloon to ensure vasodilation to enable sufficient blood flow. Tenderfoot ITC® heel incision devise will be used for heel pricks and ACCU-CHEK® Safe-T-Pro Plus lancet will be used for finger pricks. Blood samples will be stored at minus 80 °C, pending analysis. TSH, free T3, and, free T4 will be analyzed in serum using magnetic separation and detected by chemiluminescence labeled with acridinum ester on an Advia Centaur XPT (Siemens Healthcare diagnostics Inc., Tarrytown, USA). Ferritin will be analysed by an immunoturbidimetric method using Advia Chemistry XPT (Siemens Mediacal Solutions Diagnostica, Japan). Fatty acids will be analyzed in red blood cells by standardized procedures at Institute of Marine Research (IMR) [14], using ultrafast gas chromatographic (UFGC) (Thermo Electron Corporation, Massachusetts, USA). In case of advances concerning biomarkers of the primary or secondary outcome variable, other analysis than those already mentioned will be considered. This includes single nucleotide polymorphisms (SNPs) analyses from buffy coat.

### Biological samples-breastmilk

At six weeks and three months postpartum, the mothers are requested to sample breastmilk or formula. The breastmilk or formula will be analyzed for iodine content and fatty acids. Participants will receive instructions and six marked cryo tubes for collection of breastmilk at the start, during and the end of a chosen feed for two days. If the mother is not breastfeeding, she will prepare a meal of the given formula and collect in two tubes for two days. Mothers will be instructed to record date and time of sampling, and store the samples in their home freezer pending pick-up from study investigators (samples from six weeks postpartum) or submission of samples at the three months follow up visit. For submission of samples, the participants will receive freezer packs for transportation. The samples will be stored at minus 80 °C pending analysis for iodine concentration on ICP-MS, previously described by Dahl et al. [15], and fatty acids by standardized procedures at IMR [14], using ultrafast gas chromatographic (UFGC) (Thermo Electron Corporation, Massachusetts, USA).

### Biological samples-hair

Hair samples will be collected for mercury analysis from the mothers in gestational week 18 and 36, and at six months postpartum, and from infants at age six weeks, six- and eleven months. Mothers following instructions at age six weeks, will perform hair collection from infants. Samples are obtained from the mothers and infants by cutting a hair-bundle with an approximate diameter of 2–5 mm, as close to the scalp as possible from the occipital area of the head. A thin thread will be tied closest to the end nearest the scalp. Hair samples will be stored in room temperature pending analysis using Direct Mercury Analyser (DMA-80, Milestone) [16].

### Dietary intake

A structured 6-days food diary (FD), developed for this study with the purpose to estimate maternal iodine intake, will be handed out at the first visit, in gestational week 18, and mailed by post to be filled out in gestational week 35. The habitual diet of both intervention and control group is reported in a short Food Frequency Questionnaire (FFQ) in gestational week 18 and 35, and three-, six, and eleven months postpartum. The FFQ captures iodine rich foodstuff (seafood, milk, dairy, eggs and supplements), is based on a validated short seafood FFQ developed to analyze food habits in pregnant and postpartum women [17].

Infant’s dietary intake will be collected through non-validated FFQ’s (custom to the infants’ age) at three-, six- and eleven months of age. In addition, a 24-h diet recall interview will be conducted at the three- and six months’ visit. The mothers will be asked what the infant has ingested during the last 24 h. In cases of non-report of supplement intake, the mothers will actively be asked if the infant has been given any dietary supplements.

### Infant development

At eleven months, the children will be assessed with the Bayley-III by trained study investigators. The Bayley-III is a comprehensive assessment tool of neurodevelopment administered directly with the child. The tool includes three main subscales; the cognitive, language (receptive and expressive) and motor (fine and gross motor) scale. The Bayley-III represents the gold standard of developmental assessments in this age group and is widely used as an outcome measure in clinical trials. Two testers will administer the Bayley-III after undergoing training by a clinical child psychologist and a neuropsychologist. Standardization exercises will be conducted measuring the inter-rater reliability of the assessor compared with a gold standard until satisfactory level of agreement. During the trial, 10% of the tests will be double scored, and inter-rater agreement will be assessed to ensure high quality testing.

In addition, child development will be measured at three-, six- and eleven months by The Ages and Stages questionnaire, 3rd edition (ASQ-3) [18]. The ASQ-3 is an age-specific parent-reported screening questionnaire consisting of 30 items covering five developmental domains and has five subscales: communication, fine-motor, gross-motor, problem-solving, and personal-social. The scale has been translated and validated to a Norwegian setting [19].

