#### Ethics and dissemination

The trial complies with the Declaration of Helsinki, is approved by the Regional Committees for Medical and Health Research Ethics West (2015/879), and is registered in ClinicalTrials.gov (NCT NCT02610959). Infants must be especially protected in research since they do not have the competence to give informed consent and ensure that their interests are taken proper care of. Written informed consent was obtained from participants by study investigators after both written and oral information of the study. Participants can withdraw from the study at any time without giving any reason. If a participant wishes to withdraw from the study, they may require to delete collected samples and information unless the information is already included in analyzes or used in scientific publications.

It is optional to provide biological samples. All tests are performed in an age adequate way for the infants. The only invasive procedure is sampling of venous blood. Analysis have been carefully chosen regarding sample material to minimize volume drawn from the infants. Blood sampling will be performed by trained phlebotomist with experience in blood sampling of infants and children.

The mother will be informed if she or her infants’ thyroid hormone status, iron status or vitamin B_12_ status is outside the normal range and be referred to her family doctor. These parameters will be analyzed in a NS-EN ISO 15189 accredited medical laboratory and thus fulfilled the ethical considerations for notification concerning pathological blood test results. Other parameters will be analyzed at IMR in NS-EN ISO/IEC 17025 laboratories and will thus not fulfill the ethical considerations for notification concerning pathological blood test results. In addition, the samples may be analyzed a considerable time after sampling.

Results from the project will be published in peer-review journals and presented at international and national conferences. During the project period, preliminary results will be presented on conferences and seminars, both orally and as posters. Progress reports and statements will be prepared during the study and after completion, a final report for FHF partners will be prepared. A summary popular scientific article will be published in national magazines or newspapers.

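### The stated blinding does not cover the Bayley-III testers, who are described by the same role title as the staff who allocate the women

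*Protocol article*

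**What the plan says.** Three parts of the protocol article bear on this point.

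- **Who tests.** Under Infant development: "At eleven months, the children will be assessed with the Bayley-III by trained study investigators". The same section adds: "Two testers will administer the Bayley-III after undergoing training by a clinical child psychologist and a neuropsychologist". It also describes standardisation exercises against a gold standard and double scoring of 10% of tests.
- **Who allocates.** Under Randomization, allocation and blinding: "Study investigators will enroll participants, generate the allocation, and randomly assign participants to interventions after baseline sampling".
- **Who is blinded, and when.** The same section says that "participants and investigators will be blinded to the allocation until the baseline sampling has been completed". On the mothers it says: "Owing to the nature of the intervention, blinding of the participating mothers will not be possible". It then continues: "However, the infants will be blinded throughout the trial and data analysis and study investigators and laboratory personnel will be blinded when analyzing data".

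The Trial design section makes the Bayley-III cognitive, language and motor scales the secondary outcome. Trial status gives an issue date of 17 January 2018 and completion of eleven-month follow-up in September 2018.

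**The concern.** The Bayley-III is administered face to face, and the tester judges what the child can do. A tester who knows that the mother was in the cod group may, without intending to, prompt more or credit more generously. That shifts scores in one direction. A regression of score on arm cannot separate such a shift from a treatment effect, and blinding the analyst afterwards does not undo it.

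The Bayley-III is also the development measure best suited to masking. The ASQ-3 and ASQ:SE are completed by parents, and the mothers know their arm. If the Bayley-III is unmasked as well, the trial has no masked measure of infant development, although the Discussion expects the study to confirm associations between iodine and development.

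**Working it through.** No figure in the plan depends on this point, so there is nothing to reproduce. The check has two parts.

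**1. The blinding rule set against the study calendar**

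| Period | Investigators' blinding as stated |
|---|---|
| Up to the end of baseline sampling (gestational week 19) | Blinded |
| Assignment, intervention, birth, and visits up to and including the eleven-month Bayley-III | None stated |
| Data analysis | Blinded: "study investigators and laboratory personnel will be blinded when analyzing data" |

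Every Bayley-III test falls in the middle row. The only party blinded throughout the trial is the infant, who scores nothing. The mothers are not blinded.

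The stated quality measures address a different problem. Training, standardisation and double scoring show whether two raters agree. Two raters who both know the arm can agree closely and share the same bias. The double-scored sample is also small: 10% of 120 is 12 tests, and 10% of 137 is about 14.

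**2. What an observer shift would do (illustration only)**

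Inputs:
- 137 women enrolled (Trial status).
- 20% dropout and 60 per group (Sample size calculation). Applying the 20% to those enrolled gives 137 × 0.8 / 2 = 54.8, or about 55 per arm.
- Significance level 0.05 (Data analysis). The article does not say one- or two-sided, so two-sided is assumed.
- A constant shift *b* in SD units in favour of one arm. This is an assumption; the documents give no value.

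Formulas:
- Standard error of a standardised difference: SE = √(2/n). At n = 55 this is √(2/55) = 0.191. The 95% CI half-width is t(0.975; 108) × 0.191 = 0.378 SD.
- Two-sided type I error under shift *b*: Φ(−1.96 + b/SE) + Φ(−1.96 − b/SE).

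| Infants per arm | b = 0 | b = 0.1 | b = 0.2 | b = 0.3 |
|---|---|---|---|---|
| 55 | 0.050 | 0.082 | 0.182 | 0.350 |
| 60 | 0.050 | 0.085 | 0.195 | 0.376 |
| 68.5 (all 137 analysed) | 0.050 | 0.090 | 0.216 | 0.419 |

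A shift of 0.1 to 0.2 SD is about half to one standard error at 55 per arm. Keeping more infants does not help: for a fixed shift, the error rate rises with the sample size.

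**How many tests can still be protected.** Recruitment began in January 2016 at about gestational week 18 to 19. Assuming term births, the first infants reached eleven months around May 2017, and the last do so in September 2018, a span of about 16 months. The issue date falls about 8 months into it. With even recruitment, roughly half of the tests were still to come.

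**The case against.** The strongest reply is that the article condenses a fuller protocol, and that who tests which child is operational detail. Data management and biobank places the cognitive assessment forms at Uni Research Health, while the biobank is at the Institute of Marine Research, so the testers may well be a separate team. It also says that data are used only in pseudonymised form. The primary outcome is measured in the laboratory by blinded staff and is untouched.

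Part of this stands. The possibility of a separate team is real. A reader might infer that the two testers personally randomised the women or met the families at every visit. The documents do not say so; they only use the same role title. It is therefore not established that any tester knew an arm.

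The rest does not answer the point. The article does not leave blinding to another document. It sets out a scheme by party and by period, and that scheme passes over the testing visits. Pseudonymised records do not mask a person who sits with the mother and child. One could stretch the blinding at data analysis to include scoring of test forms, but that would still leave the administration of the test uncovered.

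Two further inferences should be resisted.
- The article says: "During the project period, preliminary results will be presented on conferences and seminars, both orally and as posters". A reader might conclude that between-arm results reach the testers while testing runs. The sentence gives no date and no outcome, and does not mention results by arm. A group mean would not reveal an individual child's allocation in any case.
- A reader might compare the assumed shift with the true effect to be expected. The documents give no effect size for the Bayley-III, so that comparison has no basis.

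**Conclusion.** The concern holds for the plan as written. Investigators are blinded before assignment and at analysis, the Bayley-III is done by investigators between the two, and no sentence masks the testers. This leaves the only named secondary outcome open to observer bias, which the planned training, double scoring and regression neither prevent nor remove.

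The size is unknown. The figures of 0.08 to 0.35 for the type I error at 55 per arm rest on an assumed shift of 0.1 to 0.3 SD, 20% loss from the 137 enrolled, and a two-sided test. They show how sensitive the comparison is, not what has happened. If the two testers are in fact independent and masked, the defect is one of wording and a sentence cures it. If they are not, tests already done cannot be repaired and can only be reported as unmasked.

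**What to change.** Amend Randomization, allocation and blinding and Infant development to state that the Bayley-III testers are masked to arm until all eleven-month tests are scored, and whether the two testers took any part in allocation.

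For the remaining tests, with existing staff:
- Keep the two testers away from the allocation list, the fish deliveries and the weight registration forms, or give each child to the tester who did not handle that mother.
- Ask mothers not to disclose their arm.
- Record after each test whether the tester knew or guessed the arm.
- Keep by-arm Bayley-III results from the testers until scoring is complete.

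For tests already done, record whether the tester knew the arm and report any unmasked testing as a limitation. An analysis that excludes those tests may be shown, but as exploratory only: the exclusion depends on something that happened after randomisation and may differ by arm, so it can introduce selection bias of its own.

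Two measures that might suggest themselves are not needed here. A fixed effect for tester does not remove bias from knowing the arm. Nothing here justifies holding back the urinary iodine results.

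The cost is some reassignment of tasks and one extra item on the test form. No additional assessor is needed.
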